## Abstract

**Background:**

As a meaningful subtype of ischemic stroke in Asians, Branch atheromatous disease (BAD)-related stroke is associated with high early neurological deterioration (END) and disability, but is understudied and without recommended therapy. The mechanism of END still remains unclear. Branch atheromatous disease-related stroke study (BAD-study) therefore aims to investigate demographic, clinical and radiological features, and prognosis of BAD-related stroke in Chinese patients.

**Methods/design:**

BAD-study is a nationwide, multicenter, consecutive, prospective, observational cohort study enrolling patients aged 18–80 years with BAD-related stroke within 72 h after symptom onset. Initial clinical data, laboratory tests, and imaging data are collected via structured case report form, and follow-ups will be performed at 7 days, 30 days, 90 days, 6 months and 12 months after enrollment. The primary outcome is the score on modified Rankin Scale at 90-day follow-up with single-blinded assessment. Secondary outcomes include END within 7 days, and National institute of health stroke scale score, Barthel index, cerebrovascular events, major bleeding complications, and all-cause mortality during 90-day follow-up. Characteristics of penetrating and parent artery will be assessed by high-resolution magnetic resonance imaging combined with other imaging techniques.

**Discussion:**

BAD-study can provide demographic, clinical, radiological, and prognostic characteristics of BAD-related stroke, and thereby potentially figure out the vascular mechanism of early neurological deterioration and optimize therapy strategy with the aid of advanced imaging technique. Baseline data and evidence will also be generated for randomized controlled trials on BAD-related stroke in the future.

## Background

Stroke leads to millions of death and disability in China and other countries annually [1, 2]. To optimize stroke management and improve functional outcome, causative mechanism of stroke is of great importance. Branch Atheromatous Disease (BAD), first described by Caplan in 1989 [3], is increasingly becoming a clinical entity with the aid of neuroimage, characterized by stenosis or occlusion at the origin of a penetrating artery resulting from atherosclerosis and leading to ischemic lesion [4]. In our study, the term “Branch Atheromatous Disease (BAD)-related stroke” is used for ischemic stroke due to branch atheromatous disease.

Although proposed as a meaningful concept, BAD remained neglected and underused in clinical practice, researches and guidelines for the past three decades [4]. Epidemiological data on BAD is spare, and most studies were reported in Asian population [4]. Small vessel occlusion or intracranial atherosclerosis are more common in Asians, which is different from Western populations. BAD-related stroke accounted for 9.1% in Japan and 20.4% in Hongkong among ischemic stroke patients [5, 6]. Perforating arteries involve lenticulostriate artery (LSA), paramedian pontine artery (PPA), thalamoperforating artery, anterior choroidal artery and Heubner's artery [4, 6], while what have been widely studied Is LSA and PPA, indirectly via features of ischemic lesions [4, 7]. Based on clinical and neuroimage evidence, neurologists and researchers have proposed the diagnostic criteria for BAD-related stroke [7–9].

Of patients with BAD-related stroke, the mean age ranged from 54 to 75 years, slightly younger than that in large artery disease (LAD) or lacunar infarction (LACI), and male gender was more prevalent [4, 6, 10]. The median National Institutes of Health Stroke Scale (NIHSS) score of BAD-related stroke was 4, lower than 6 in LAD, but similar with that in LACI. The short-term disability (modified ranking scale [mRS] ≥ 3) rates of LAD, BAD-related stroke, and LACI were 74%, 61%, and 47%, respectively [6]. However, long-term outcomes were comparable between BAD-related stroke and LACI [11]. Finally, the clinical, neuroradiologic, and predictive data are insufficient for BAD-related stroke.

One challenge of BAD-related stroke was its high incidence of early neurological deterioration (END) [5, 12], which was strongly associated with poor outcome [13]. Compared with distal single subcortical infarction, BAD-related stroke showed higher-volume lesion (median, 1.79 vs 0.44 ml) and more frequent END [10, 14–16]. The rate of END following intravenous thrombolysis was estimated as 13.8%, measured by the deterioration of NIHSS score at 24 h (≥ 4) [12]. Intravenous thrombolysis seemed unable to prevent END and controversial about its effect on improving functional outcome among patients with BAD-related stroke [12, 17–19]. In addition, Seners P, et al. found that strongest predictors for END were consistent across thrombolysed and non-thrombolysed acute ischemic stroke patients including hyperglycemia, proximal arterial occlusion, large infarcts, no recanalization or re-occlusion, and etc. [12]. Thus, preventing the progression of stenosis and re-occlusion of proximal penetrating artery has become the essential node of the early management of BAD-related stroke. Multiple studies focused on the mechanism of END due to unique brain ischemia with poor collateral circulation [20]. However, no evidence-based therapy was recommended for secondary preventive treatment in acute phase of BAD-related stroke.

Previous study found that dual-antiplatelet or anticoagulation therapy might reduce END, but their effect on BAD-related stroke remained unclear and might increase the risk of bleeding [21, 22]. Tirofiban also showed efficacy on reducing END and improving outcomes in patients with endovascular therapy, intravenous thrombolysis or BAD-related stroke, but warranting further confirmation in large-sample patients with BAD-related stroke [23–25]. The optimal regimen for reducing END and improving outcome remains inconclusive [19].

In addition, many researchers focused on the role of inflammatory indicators in stroke pathogenesis and prognosis, including the effect of white blood cell, platelet, lipid level and etc. [12, 26–28]. For instance, a randomized controlled study reported that high-dose statins could reduce the level of inflammatory indicators and improve the outcome of ischemic stroke [29]. Elevated high-sensitivity C-reactive protein and inflammatory indicators also predicted poor outcome of stroke [30, 31]. However, the effect of inflammatory indicators on BAD-related stroke was unknown.

Another advance in BAD-related stroke is the application of high-resolution magnetic resonance imaging (HR-MRI) and images of vessel wall, which facilitates visualized analysis of LSA, PPA and their parent arteries [32, 33], and the further research of vascular pathophysiology of BAD-related stroke and END.

Although neurologists increasingly consider BAD-related stroke as a clinical entity and a subtype of ischemic stroke with relatively poor outcome, its demographic, clinical and radiological characteristics are still lacking with little evidence of therapy. Therefore, we describe here the protocol of BAD-study, a multicenter prospective cohort study in China to investigate demographic, clinical, radiological features, risk factors, and prognosis of BAD-related stroke and explore the optimal regiment for good outcome.

## Methods/design

### Study design

BAD-study is a nationwide, multicenter, consecutive, prospective, observational, cohort study recruiting patients with BAD-related stroke within 72 h after symptom onset. Due to February 28, 2022, this ongoing study has recruited 22 hospitals with the equipment of 3 Tesla (T) magnetic resonance imaging, with the leader of Peking Union Medical College Hospital in Beijing, China. BAD-study was approved by the Ethics Committee of Peking Union Medical College Hospital on May 25, 2021 (No. ZS-2982B), and written informed consents (model consent form) are required for all patients. In addition, protocol modifications, if any, would be approved by the ethics committee. The anticipated duration of the study will be about 2 years from June 1, 2021 until May 31, 2023. BAD-study has been registered on July 28, 2021 at clinicaltrials.gov, with identifier NCT04973774.

### Study objectives

The primary objective of this study is to figure out the demographic, clinical, radiological characteristics, risk factors, and prognosis of BAD-related stroke in this clinical-radiological cohort with large sample, and evaluate the effects of different real-word therapies on outcome. Secondary objectives are to: 1) investigate the vascular mechanism of END; 2) establish the association between clinical, clinical, radiological characteristics and clinical outcome and model for predicting outcome; 3) find out the standardized process and criteria for analyzing penetrating arteries using vessel wall imaging (VWI) based on 3 Tesla-MRI; 4) explore the efficacy of safety of specific drugs, such as aspirin and tirofiban, providing baseline data for further clinical trials.

### Study population

All consecutive ischemic stroke patients aged 18–80 years visiting any center of our study considering BAD-related stroke will be screened for eligibility according to the following inclusion and exclusion criteria. All eligible patients will be Invited to participate in this observational study.

Inclusion criteria:1. Age:18–80 years.2. Acute cerebral infarction, if the clinical manifestations are transient, new infarct lesion should be found on Diffusion Weighted Imaging (DWI) at the same time.3. The time from symptom onset to enrollment is less than 72 h. If the onset time was unknown, the time of last known free of new ischemic symptoms to enrollment is less than 72 h.4 Meet all the following radiological criterial:1) DWI lesion: single (isolated) deep (subcortical) infarct;2) The culprit vessels are the LSA or PPA, and the infarct lesion on DWI conforms to one of the following characteristics (A/B):A. LSA: (1) “Comma-like” infarct lesions with “Fan-shaped” extension from bottom to top in the coronary position; OR (2) ≥ 3 layers (layer thickness 5–7 mm) on axial DWI images of the head;B. PPA: the infarct lesion extends from the deep pons to the ventral pons on the axial DWI of the head.3) No ≥ 50% stenosis on the parent artery of the criminal vessel (i.e. corresponding basilar or middle cerebral artery) (confirmed by magnetic resonance angiography [MRA] or computed tomography angiography [CTA] or digital substraction angiography [DSA]).5 Signed informed consent by the patient or legally authorized representatives.Exclusion criteria:1. Intracranial hemorrhagic diseases, vascular malformations, aneurysms, brain abscesses, malignant space occupying lesions or other non-ischemic intracranial lesions observed by baseline head CT and MRI, MRA/CTA/DSA.2. There was ≥ 50% stenosis of extracranial vessels with ipsilateral serial relationship.3. Cardiogenic embolism: atrial fibrillation, myocardial infarction, valvular heart disease, dilated cardiomyopathy, infective endocarditis, atrioventricular block disease, heart rate less than 50 beats /min.4. Have received or plan to receive acute endovascular treatment after onset of the disease.5. Stroke caused by other clear causes, such as moyamoya disease, arterial dissection, vasculitis, etc.6. mRS score prior to the onset of the disease was ≥ 2 points.7. Known malignant tumor.8. Life expectancy ≤ 6 months.9. Contraindications of 3 T MRI examination.10. Pregnant or lactating women.11. Participation in another clinical within 3 months before enrollment, or taking part in another ongoing study.

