### Procedures

The board of primary investigator, neurologists, radiologists, epidemiologists, pharmacologist and statisticians was established on June 1, 2021. All hospital personnel have been trained on the reading of neuroimages in screening stage, the collection of data at baseline and each follow ups, and etc. The enrollment of first case in each center will be confirmed by the board. Eligible patients will be recruited at the time of signing the informed content. Baseline data included demographic and clinical assessments, neuroimages and laboratory data (first ones after stroke onset). Follow-ups will be conducted at 7 days, 30 days, 90 days, 6 months, and 12 months after enrollment, via face-to-face interviews or telephone, when the mRS, cerebrovascular events, adverse effects of medications, and etc. will be evaluated. At the follow-up of 7 days, the event of END will be assessed since stroke onset. The 90-day follow-up is required to be assessed by the neurologists, who are blinded to the clinical, radiological characteristics and treatment of selected patients. The flowchart of BAD-study is shown in Fig. 1.

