### Outcome measures

The primary outcome in our study is the score on the modified Rankin scale at 90 days, which is a 7-point scale ranging from 0 (no symptoms) to 6 (death) [36]. Secondary outcomes include END within 7 days, and NIHSS score, Barthel index, cerebrovascular events (myocardial infarction, new-onset ischemic stroke, new-onset intracranial hemorrhage), and major bleeding complications measured by PLATO (Platelet Inhibition and Patient Outcomes) definition during 90-day follow-up [37]. All-cause mortality within 90 days is also recorded. The follow up times are extended to 1 year, as the long-term outcome of BAD-related stroke remains inconclusive [4, 6].

The END is defined as: 1) From symptom onset to 7 days after enrollment; and 2) Occurrence of deterioration of neurologic deficits after initial assessment: A. An increase of the NIHSS score ≥ 4 points or the NIHSS motor score ≥ 1 point for ischemic patients; or B. The stereotyped attacks still repeat ≥ 3 times after arrival at hospital or progress to persistence status for patients with internal capsule warning syndrome or pontine warning syndrome [12, 38].

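### The DWI scan that decides eligibility is not fixed in time relative to early neurological deterioration (END), so the END rate can be inflated and lesion extent can be a result of END

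*Protocol article*

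**What the plan says.** **Entry.** Under Study population, inclusion criterion 3 sets the window: "The time from symptom onset to enrollment is less than 72 h". Criterion 4 starts with "DWI lesion: single (isolated) deep (subcortical) infarct", which does not depend on extent. The next item does. For LSA it asks for a comma or fan shape, or at least three layers ("layer thickness 5–7 mm) on axial DWI images of the head"). For PPA it asks that "the infarct lesion extends from the deep pons to the ventral pons on the axial DWI of the head". None of these items names the scan on which it is read, or requires that scan to come before any worsening.

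**Outcome.** Under Outcome measures: "The END is defined as: 1) From symptom onset to 7 days after enrollment", with "Occurrence of deterioration of neurologic deficits after initial assessment". The initial assessment is not tied to the DWI that decides eligibility. Part B of the definition counts, among other things, patients who "progress to persistence status for patients with internal capsule warning syndrome or pontine warning syndrome". Procedures has END assessed at the day-7 visit, looking back to stroke onset.

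**Baseline images.** Procedures lists "neuroimages and laboratory data (first ones after stroke onset") among the baseline data.

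**Timing.** Table 3 gives a median of 48 h (IQR 30–65) from onset to enrolment in the first 143 patients. Table 1 collects the times of onset, arrival, enrolment and END, and lists no scan time.

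**The concern.** END can occur after the initial assessment but before the scan on which the patient qualifies, and the plan counts it. Suppose two patients each have a first DWI one layer short of the LSA criterion. One worsens, is scanned again, now shows three layers, enrols, and is an END case. The other stays stable, may have no second scan, and may never be enrolled. Patients who enter by the first route are all END cases. They add equally to numerator and denominator, and so raise the rate.

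The second consequence concerns predictors. If lesion extent comes from a scan taken after END, it may reflect growth during the deterioration. Using it to predict END would then reverse cause and effect.

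END is a named secondary outcome and its vascular mechanism is the first secondary objective. The Discussion also plans to analyse lesion volume and to compare therapies on END. Analysis cannot recover patients who were never enrolled, but it can separate those who entered after END, provided scan times are recorded.

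**Working it through.** **No plan figure to reproduce.** The article states no expected END rate for this cohort. Its one design figure, 450 × 1.10 = 495, rests on a count of variables and does not bear on this point.

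**Step 1: is the sequence possible?** Enrolment may be up to 72 h after onset. With a lower quartile of 30 h and a median of 48 h, about three quarters of the first 143 patients had at least 30 h, and half had at least 48 h, in which END could occur before enrolment and still count. The time of the qualifying DWI is not given. The sequence worsen, scan, qualify, enrol, count as END is therefore allowed by the text, but its frequency is unknown.

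**Step 2: simple illustration, all inputs assumed.** Take 100 patients. On the first scan 70 meet the extent criterion (END risk 20%, so 14 cases) and 30 fall short. Half of the END cases among those 30 later qualify, and none of the stable ones do.

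| Assumed END risk in the 30 who fall short | Later entrants | Observed END rate |
|---|---|---|
| 20% | 3 | (14 + 3)/(70 + 3) = 23.3% |
| 10% | 1.5 | (14 + 1.5)/(70 + 1.5) = 21.7% |
| 5% | 0.75 | (14 + 0.75)/(70 + 0.75) = 20.8% |

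The lower risks are the more plausible: the Background reports smaller lesions and less frequent END in distal single subcortical infarction than in BAD-related stroke.

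**Step 3: general form.** Let p be the END risk in patients who meet the criterion before any deterioration. Let s be the number of below-threshold patients per such patient, and q their END risk. Let g be the share of their END that precedes the qualifying scan and carries the lesion over the threshold. Then

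observed rate = (p + s·q·g) / (1 + s·q·g).

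The only END rate in the article is 13.8% (24 h after thrombolysis, NIHSS rise of at least 4). It comes from another population and definition, and serves here only as a low anchor. The values p = 25% and 35%, s = 0.5 to 2, q = 5 to 10% and g = 0.25 to 0.50 are assumptions.

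- Smallest addition: s·q·g = 0.5 × 0.05 × 0.25 = 0.00625.
- Largest addition: s·q·g = 2 × 0.10 × 0.50 = 0.10.

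| p | Smallest addition | Largest addition | Rise (points) |
|---|---|---|---|
| 13.8% | 0.14425/1.00625 = 14.3% | 0.238/1.10 = 21.6% | 0.5 to 7.8 |
| 25% | 0.25625/1.00625 = 25.5% | 0.35/1.10 = 31.8% | 0.5 to 6.8 |
| 35% | 0.35625/1.00625 = 35.4% | 0.45/1.10 = 40.9% | 0.4 to 5.9 |

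With g = 0 the observed rate equals p and there is no inflation.

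**The case against.** The strongest reply is that the text is only silent on the deciding scan, and that the article does not show a bias. It describes no re-scanning after worsening, no first scans that fall short and no lesion growth past a threshold, and screening is said to be consecutive. This stands: a reader might infer that END in fact makes patients eligible and that the rate is inflated, but the documents support only that it can be.

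The note in Procedures about first data after onset, and exclusion 1, which is read on baseline CT and MRI, suggest that the first scan is the screening scan. This has some force. But the note may cover laboratory tests alone, and it describes baseline data, not the scan that decides eligibility. A first scan may also itself follow deterioration. The route stays open.

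A condensed article may leave index-scan procedures to the full protocol. Even so, the criteria and the END window as printed leave the two unordered, and that is enough to ask for scan times.

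Two further strong readings fail:

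- A reader might infer that warning-syndrome patients enrol only if they progress. Criterion 2 admits transient presentations with a new DWI infarct, so patients whose attacks stop can enter. END part B also counts repeated attacks after arrival without a persistent deficit.
- A reader might infer that the association of lesion extent with END is necessarily exaggerated. A post-END scan can strengthen it, but restricting entry to extended lesions can weaken it, so the direction is unsettled. Plaque site, stenosis and vessel wall, on which the mechanism objective largely rests, are not shown to change with infarct growth.

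**Conclusion.** The point holds in a limited form. Eligibility depends on lesion extent on an unspecified DWI, and END before enrolment counts, so entry can depend on the outcome and the END rate can be too high. Lesion extent measured after END may be its result.

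Under the assumed ranges the rise is 0.4 to 7.8 percentage points. In the simple illustration, a true 20% becomes about 21 to 22% when below-threshold patients carry a 5 to 10% END risk. Larger shifts need stronger assumptions. For example, if half of all patients fall short at the same 20% risk and every one of their END cases qualifies, the rate is (10 + 10)/(50 + 10) = 33.3%. That would need each of those events to occur before enrolment, although END is counted to 7 days after it.

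The effect is zero if the qualifying scan always precedes END. It is diluted if stable patients are also re-scanned and qualify. The documents give no scan times or re-scan rates, so the true size cannot be stated and may be small. The primary outcome, 90-day mRS, is not the subject of this point.

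**What to change.** Leave the eligibility criteria unchanged. Restricting criterion 4 to the first DWI would make later-qualifying patients ineligible, and would still miss a first scan taken after END.

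1. Record the date and time of the DWI on which the patient qualified, and of the first DWI if it is a different scan.
2. Compare both with the END time already collected in Table 1.
3. In the END-rate and END-predictor analyses, exclude or report separately patients whose qualifying DWI followed END. Showing the rate with and without them makes the dependence visible. They stay in the descriptive cohort.
4. As predictors of END, use only lesion measures from scans taken before END.

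The cost is one or two time fields in the eCRF, retrieval of scan times for patients already enrolled (143 by March 13, 2022), and the loss of some patients, including END cases, from the END analyses.

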### Procedures

The board of primary investigator, neurologists, radiologists, epidemiologists, pharmacologist and statisticians was established on June 1, 2021. All hospital personnel have been trained on the reading of neuroimages in screening stage, the collection of data at baseline and each follow ups, and etc. The enrollment of first case in each center will be confirmed by the board. Eligible patients will be recruited at the time of signing the informed content. Baseline data included demographic and clinical assessments, neuroimages and laboratory data (first ones after stroke onset). Follow-ups will be conducted at 7 days, 30 days, 90 days, 6 months, and 12 months after enrollment, via face-to-face interviews or telephone, when the mRS, cerebrovascular events, adverse effects of medications, and etc. will be evaluated. At the follow-up of 7 days, the event of END will be assessed since stroke onset. The 90-day follow-up is required to be assessed by the neurologists, who are blinded to the clinical, radiological characteristics and treatment of selected patients. The flowchart of BAD-study is shown in Fig. 1.

